
## Study objectives

The manualised Stress-Traumasymptoms-Arousal-Regulation-Treatment (START) programme was developed from clinical work with traumatised unaccompanied refugee minors in Germany to promote coping with traumatic distress and emotional irritability.^18–20^ An uncontrolled pilot study in 22 traumatised refugee minors showed positive effects on emotion regulation, adaptive strategies, self-control, distress and good feasibility.^18^ A subsequent study confirmed the positive effects on adaptive emotion regulation strategies.^21^

The primary aim of this RCT is to evaluate the efficacy of the START programme in reducing psychological distress and trauma symptoms in traumatised adolescent refugees compared with a waiting-list control group (WL). Main secondary aims are to assess whether treatment effects will remain stable for at least 12 weeks after programme termination (follow-up at week 24) and to assess whether the participants of the START groups improve emotion regulation strategies and mental health compared with WL. As stress and emotions are context-dependent and highly dynamic,^22^ intervention effects are assessed by psychometric instruments and with electronic ambulatory assessment (e-diaries). Ambulatory assessment aims to reduce retrospective biases while gathering ecologically valid data from everyday life near real-time. It has been shown as superior to retrospective psychometric assessment in terms of predicting symptom and treatment outcome^23–26^ and assessing reliably everyday functioning.^27^ We also evaluate intervention effects on the neuroendocrine stress system by assessing hair cortisol, which reflects the cumulative cortisol release over the past months and has been shown to capture treatment effects in PTSD.^28^

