### Trial design and setting

The study is conducted as a 12 weeks, two-arm, randomised, WL-controlled, multicentre trial with a 12-week follow-up and six participating outpatient departments in Germany, all of which are experienced in treating traumatised adolescent refugees. The study is coordinated by the Department of Child and Adolescent Psychiatry and Psychotherapy, University Medical Center, Johannes Gutenberg University, Mainz, Germany. The study intervention comprises an adapted version of the START programme.^18–20^ Languages used in the study for the intervention and the assessments are Arabic, Dari, English, German or Somali. Interpreters are involved if needed. The study is not blinded for the treatment condition, which will be evident to participants, caregivers and study therapists. Recruitment started 1 October 2020. We expect that the last participants will complete the study end of October 2022. Data base lock and analysis of primary outcomes are planned until end of December 2022.

Key stopping rules for patients are a withdrawal of informed consent, unwillingness to further participate in the trial, any factors affecting the patient’s or others’ well-being, for example, acute suicidality or acute endangerment to others, onset of other acute severe mental disorders, alcohol or substance abuse, inpatient treatment of over 2 days, start of concurrent psychotherapy and more than two psychotherapeutic crisis interventions. Key stopping rules for participating centres are non-adherence with the International Council for Harmonisation of Technical Requirements for Pharmaceuticals for Human Use: Guidelines for Good Clinical Practice (ICH-GCP)^32^ or the study protocol, insufficient recruitment of participants, or insufficient data quality. The key stopping rule of the trial is a change in the overall risk-benefit ratio.

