### Trial flow

For a summary of trial flow and assessment visits please see the SPIRIT flow diagram, table 1. All assessments are provided by trained study staff and are performed at the screening visit, baseline (T0), post-treatment (after 8-week START programme or 8-week waiting time; T1), after the booster session or 12-week waiting time (T2), and after 24 weeks at the 12-week follow-up (T3). The maximum time allowed between T0 and T3 is 26 weeks. After termination of the study, all participants are informed about their current diagnostic status and available interventions provided by child and adolescent psychiatric and psychotherapeutic routine care. Participants of the WL are given the opportunity to take part in independent START groups.

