#### Baseline (T0), post-treatment (T1), booster session (T2), 12-week follow-up (T3) assessments

T0 takes place between one and 2 weeks after randomisation (WL) or before the first programme session (START), T1 within 1 week after the 8-week programme (START) or within 8–9 weeks after T0 (WL), T2 within 1 week after the booster session (START) or 4–5 weeks after T1 (WL) and T3 follow-up visits within 12 weeks after T2 (START/WL). At T0 only, the Post-Migration Living Difficulties Questionnaire (PMLD) and Questionnaire on Therapy Expectation are assessed. At the T0(T1)–T3 visits primary endpoints, trauma symptoms, emotion regulation, general psychopathology, overall clinical severity of mental disorders, suicidality and endangerment to others are assessed and 1 week e-diaries are applied. Hair cortisol is assessed at T0, T2 and T3. Adverse events are assessed at T0–T3 visits and weekly until T1.

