### Analysis population and analysis

All randomised participants will be included in the full-analysis set as allocated. All randomised participants, who finish the study according to the study protocol until T2 as planned with no missing values for T1 (primary endpoint) will be included in the per-protocol set for analysis as allocated. All randomised participants will be included in the safety population according to the applied intervention.

Baseline characteristics will be analysed descriptively for the safety, full-analysis, and per-protocol set in the intervention and control group. The primary and coprimary endpoints will be analysed in the full-analysis set. Missing values will be imputed. Endpoints will be assessed as response variables in linear mixed regression models with site and psychotherapeutic group as random effects, intervention group, sex and region of origin as fixed effects, and age, PSS-10 and IES-R baseline scores, respectively, as linear effects with a hierarchical testing procedure that maintains the overall significance level of *α*=0.025. The primary analysis will be repeated in the per-protocol population as a sensitivity analysis. Since the different timing of the T0 baseline examination in the study groups after randomisation could cause biases in the effect estimates, that cannot be estimated or modelled, additional sensitivity analyses will be performed, such as repeating the primary analysis using the screening value instead of the baseline value. Secondary outcomes will be analysed in the full-analysis set. Missing values will not be imputed. The stability of treatment effects up to T3 will be assessed by calculating confidence intervals on the T1–T3 and T2–T3 difference for the PSS-10 and IES-R total scores in the intervention group. Psychometric scales used for assessment of secondary outcomes and hair cortisol concentrations will be analysed according to primary endpoints or descriptively. For the analysis of e-diary data, multilevel models will be used to characterise momentary mechanisms and context-dependent affective experiences, which allow a nested data structure (momentary experiences within participants), and enable different numbers of ratings per participant to be handled quite well.^71^ Safety variables will be analysed in the safety and full-analysis population.

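### The planned within-START intervals do not show whether the START–WL treatment effect persists to T3, which is one of the main secondary aims

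*Protocol article*

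**What the plan says.** Under Study objectives, the primary aim is efficacy "in traumatised adolescent refugees compared with a waiting-list control group (WL". One of the main secondary aims is to "assess whether treatment effects will remain stable for at least 12 weeks after programme termination (follow-up at week 24". The other concerns emotion regulation and mental health, and is explicitly a comparison with WL.

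Under Analysis population and analysis, stability to T3 is to be assessed by "confidence intervals on the T1–T3 and T2–T3 difference for the PSS-10 and IES-R total scores in the intervention group". For secondary outcomes, analysed in the full-analysis set, the same paragraph says just before this: "Missing values will not be imputed". The primary endpoints, by contrast, are analysed with imputation in all randomised participants, in a mixed model with intervention group as a fixed effect.

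Both arms are followed: "T3 follow-up visits within 12 weeks after T2 (START/WL". The assessment section reads "At the T0(T1)–T3 visits primary endpoints, trauma symptoms, emotion regulation, general psychopathology", and Table 1 marks PSS-10 and IES-R at T1, T2 and T3. Under Trial flow, a sentence about what happens once the study has ended is followed by: "Participants of the WL are given the opportunity to take part in independent START groups". Under Trial design and setting, the patient stopping rules include "start of concurrent psychotherapy and more than two psychotherapeutic crisis interventions".

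**The concern.** The treatment effect in a waiting-list trial is a difference between arms. Whether it lasts depends on what both arms do after T1. The stated analysis looks at one arm, so it mixes persistence of the effect with the natural course of symptoms, and the randomised comparator measured at the same visits plays no part.

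This can mislead in two directions. If WL participants catch up while START participants hold steady, a shrinking or vanished effect is reported as stable. If symptoms in both arms worsen together, for instance through changes in asylum status or living conditions, a fully maintained effect is reported as lost. A claim of durability would rest on an uncontrolled before–after comparison inside a randomised trial.

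Without imputation, a T1–T3 change can be formed only for START participants seen at both visits. The article does not name this as an observed-case analysis, but it follows from the sentence on missing values.

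**Working it through.** **The plan's own figures.** The article gives no figure for the stability analysis. Its sample size reproduces closely. A two-sample t-test at one-sided α = 0.025 with 80% power and equal arms gives 82 for d = 0.63 (stated 84) and 104 for d = 0.56 (stated 104). Then 104/(1 − 0.40) = 173.3, hence 174. Sample size is not in dispute. The allocation ratio is not stated; 1:1 (87 per arm) is assumed here.

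**What is needed and what is estimated.** Let S and W be the mean scores in START and WL, in SD units, with higher scores worse. The treatment effect at visit t is D(t) = W(t) − S(t). Its change is

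D(T3) − D(T1) = [W(T3) − W(T1)] − [S(T3) − S(T1)].

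The planned interval estimates only the second bracket.

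**START flat.** Put S(T3) − S(T1) = 0 and start from the planned effects. The WL improvements are illustrative, not forecasts.

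| WL improvement T1–T3 (SD) | Centre of planned interval | IES-R effect at T3 | PSS-10 effect at T3 |
|---|---|---|---|
| 0 | 0 | 0.56 | 0.63 |
| 0.2 | 0 | 0.36 | 0.43 |
| 0.3 | 0 | 0.26 | 0.33 |
| 0.4 | 0 | 0.16 | 0.23 |
| 0.56 | 0 | 0.00 | 0.07 |

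The planned analysis gives the same answer in all five rows.

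**Common drift.** Suppose both arms worsen by 0.3 SD. D(T3) − D(T1) = 0.3 − 0.3 = 0, so the effect is intact. The within-START interval centres on a worsening of 0.3. With the half-width of 0.24 derived next, it runs from 0.06 to 0.54 and excludes zero.

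**Precision of the two analyses.** The inputs are n = 87 × 0.60 ≈ 52 per arm, with equal SDs and T1–T3 correlation ρ, ignoring therapy-group clustering and covariates. The SD of a change is √[2(1 − ρ)]. At ρ = 0.6 (assumed):

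- within START: 1.96 × √0.8/√52 = 0.24 SD
- change in the START–WL difference: 0.24 × √2 = 0.34 SD

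For ρ from 0.7 to 0.3 the ranges are 0.21 to 0.32 SD and 0.30 to 0.46 SD. The 52 reflects the planned 40% loss by T1 only; no T1–T3 loss is given. With 43 per arm the ranges become 0.23 to 0.35 and 0.33 to 0.50 SD; with 35 per arm, 0.26 to 0.39 and 0.36 to 0.55 SD.

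**The contrast at T3 itself.** The half-width is 1.96 × √(2/n), and power is Φ(d√(n/2) − 1.96).

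| Retained at T3 (assumed) | n per arm | Half-width (SD) | Power, d = 0.56 | Power, d = 0.63 |
|---|---|---|---|---|
| 60% | 52.2 | 0.38 | 82% | 90% |
| 50% | 43.5 | 0.42 | 74% | 84% |
| 40% | 34.8 | 0.47 | 65% | 75% |

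**The case against.** **The contrast may already be covered.** The abstract lists intermediate programme effects at follow-up among the secondary outcomes, and the analysis section says scales for secondary outcomes are analysed like the primary endpoints or descriptively. A T3 comparison is therefore not excluded, and the full protocol is not shown. But PSS-10 and IES-R are the primary scales, their stability has its own sentence, and the alternative of a descriptive analysis commits to nothing. What stands is that the article cannot be said to rule out any between-arm look at T3. It is the stated stability analysis that does not provide one.

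**Stability may mean maintenance of gains in treated participants.** The planned intervals do describe that. The stated aim, however, is stability of treatment effects, in a trial that defines efficacy against WL.

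**WL may not be a clean comparator at T3.** The sentence offering START to WL carries no date; the timing comes from the sentence before it. The waiting time is elsewhere given as 12 weeks, and the flow figure is not available. The natural reading is still that WL has had no START by T3. Stopping patients who begin other psychotherapy supports an untreated control, but may leave a selected group in either arm. That is a reason to state a missing-data assumption.

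**Stronger readings that a reader might infer.**

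- *The aim cannot be answered.* The documents do not support this: both arms are measured at T3, so the fault lies in the analysis and not in the data collected.
- *A particular weekly rate of natural improvement in WL.* The article gives none, and its background section reports a high risk of chronic problems. The point does not depend on a rate.
- *The planned interval is too imprecise, since 0.24/0.56 = 43% of the planned effect.* This does not favour the remedy, whose interval for the change is wider: 0.34/0.56 = 61%. The objection is to what is estimated, not to its precision.
- *Effect and stability come from different people.* START participants seen at T1 and T3 are a subset of the full-analysis set.

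**Conclusion.** The point holds for the stated stability analysis. Within-START changes without imputation do not show whether the START–WL effect persists to T3. Followed exactly, the rule gives the same result whether the T3 effect on IES-R is 0.56 SD or zero, provided START is flat, and it can report loss when both arms drift together. This follows from the identity for D(T3) − D(T1) and needs no assumed rate of natural change.

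The scope is limited. It concerns one of the main secondary aims, for which intervals and no hypothesis test are planned. The primary T1 comparison, the sample size and the other main secondary aim are unaffected. The conclusion rests on WL not receiving START before T3, which is the natural reading of Trial flow but is not stated in one sentence. The precision figures additionally assume 1:1 allocation, the T3 retention shown, the correlation shown, and no allowance for clustering.

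**What to change.** Make the stability analysis a START–WL contrast of PSS-10 and of IES-R at T3, together with its change from T1, each with a confidence interval. Obtain both from one likelihood-based repeated-measures model per scale at T1, T2 and T3 in the full-analysis set. Include arm-by-visit terms, the covariates and random effects of the primary model, and within-participant correlation between visits. State the missing-at-random assumption on which it rests. Keep the within-START T1–T3 and T2–T3 intervals as description, and confirm in the text that WL participants receive START only after T3.

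The cost is protocol or analysis-plan wording and one extra model, with no new data. The price in precision is the wider interval for the change in the between-arm difference, about 0.34 SD against 0.24 SD under the assumptions above and wider with further loss by T3. The results should therefore be reported as an estimate with its interval, and an interval that includes zero should not by itself be read as proof of stability.

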### Ethics and dissemination

The study protocol, patient recruitment procedures, patients’ information and informed consent material have been approved by the lead ethics committee of Rhineland-Palatinate (ID 2019-14709) and the ethics committees of participating sites. For every substantial protocol modification approval of all ethics committees is required. The study will be conducted according to ICH-GCP^32^ and the Declaration of Helsinki.^67^ Study results will be published through peer-reviewed publications and presented at scientific and clinical conferences.

## Trial status

Recruitment started 1 October 2020.

## Discussion

Evidence-based, evaluated, low-threshold and culture-sensitive psychotherapeutic treatment programmes, that reduce distress caused by traumatic experiences that can be efficiently established in routine mental healthcare, would represent valuable therapeutic interventions to support refugee minors with trauma-related symptoms and emotion regulation difficulties. However, such interventions are currently lacking. The primary aim of this study is to evaluate the clinical efficacy and intermediate outcome of the distress-reducing psychotherapeutic START programme and to contribute to improved evidence-based therapeutic interventions for adolescent refugees within a stepped-care mental health approach in Germany. If shown to be effective, the first rigorously evaluated manualised intervention programme for traumatised adolescent refugees will be available, which will have widespread implications for clinical practice.

Some limitations for the application of the programme in mental health routine care in host countries may be that the therapeutic study groups are limited only to traumatised refugees, which may not reflect clinical reality. Another limitation is the restriction of study participation to refugee minors with language skills in Arabic, Dari, English, German and Somali. Thus, the study will not provide information on the effectiveness of the programme if applied to refugee minors with a different cultural or language background. However, since all programme materials are available in Arabic, Dari, English, German and Somali, the START programme will provide a treatment option not only in German-speaking or English-speaking host countries that care for refugee minors but also in refugee camps based in Arabic-speaking, Dari-speaking or Somali-speaking countries, where is a huge need for easy-to-apply psychotherapeutic treatment options.

Beyond effects on the symptom level, we will analyse intervention effects on psychosocial functioning and everyday behaviour through the use of e-diaries and on the neuroendocrine stress system by analysing hair cortisol. The multimodal assessment approach of symptoms, functioning, daily living outcomes, context variables and neuroendocrine effects, as well as the follow-up assessment, will enable us to analyse immediate and intermediate treatment effects not only on the phenomenological clinical level but also on the biological and daily living level. This will extend our understanding of intervention effects, influencing factors and the course of trauma-related mental health problems in refugee minors.
